#### Blinding

The blinding strategy utilized in this clinical trial follows guidelines previously set forth and designed specifically for non-pharmaceutical intervention trials [51]. As recommended [52], research design elements such as treatment type, active and inactive treatment mechanisms, and research hypotheses are concealed from participants, testing administrators, and data collectors. Active and sham treatment allocation is concealed from the participants and testing administrators. Both testing administrators and study participants will be told that they will provide/receive two different *versions* of nerve stimulation at different locations on the ear (for the tVNS group) or that there are two breathing techniques that are being explored (for the MNRB group) in this investigation [53]. The testing administrators will introduce either “Version 1” (active) or “Version 2” (sham) of the treatment interventions.

The principal investigators ([name] and [name]) are blinded to patient treatment allocation as well as the randomization form in Viedoc. This form will only be visible to the testing administrators performing participant data collection. To protect against export of blinded data during the study, there will be two export roles in this study: (1) blinded export and (2) unblinded export. Blinded data export role will be given to the investigators prior to database lock while the unblinded data export role will be given to the investigators only after database lock.

#### Statistical considerations and sample size calculation

An independent trial statistician who is blinded to the treatment allocation will complete the initial analysis for the main outcomes. Data analyses will be performed using IBM SPSS version 25, R software, and SAS® software after importing data from Viedoc. To sufficiently detect a difference between groups in HRV as it relates to NRS pain intensity, a sample size between 30 and 77 (depending on the HRV metric used) is typically needed [54]. However, subgroups are commonly employed within designs that have been suggested to require 20 participants per cell [55]. Furthermore, researchers have typically used Cohen’s calculations of small (0.2), medium (0.5), and large (0.8) effect sizes when quantifying the magnitude of group differences for HRV investigations. However, it has been recommended that these guidelines should only be used when the effect size distribution (ESD) is unknown; analyses have shown that Cohen’s guidelines underestimate the magnitude of small and large effect sizes and that HRV studies are generally underpowered [56]. A change on the NRS of 20% as our secondary outcome measure in this study for participants between CVI and CVII will be considered to be a clinically significant treatment efficacy [57, 58].

Due to our power calculation and in light of these findings, effect sizes of 0.25, 0.5, and 0.9 should be interpreted as small, medium, and large effects (after rounding to the closest 0.05). To achieve a statistical power of 0.8 to detect a large effect size, 21 participants are required per group in a case-control study [56]. However, in order to account for possible participant dropout, 28 participants per group will be included which correlates to a statistical power of 0.9. This recommended sample size which is based upon the aforementioned ESD can be tailored to our specific study used to appropriately power this research investigation [56]. This makes it more likely to better replicate and derive true effect size estimates. Mean with standard deviation or median with interquartile will be reported for continuous variables/data. Frequency and percentage will be given for categorical variables/data.

Missing data will be treated as follows: If the first (morning pre-intervention) NRS/HRV recording is missing, the last (evening post-intervention) NRS/HRV recording will be used from the night before. If the second (morning post- intervention) NRS/HRV recording is missing, then the first (morning pre-intervention) NRS/HRV recording will be used. If the third (evening pre-intervention) NRS/HRV recording is missing, then the first (morning pre- intervention) NRS/HRV recording will be used. Finally, if the last (evening post-intervention) NRS/HRV recording is missing, then the third (evening pre-intervention) NRS/HRV recording will be used. If all morning and evening NRS/HRV recordings are missing from a day, then NRS/HRV recordings from the day before will be used based upon the assumption that improvement/change is not present. The patient-reported outcome measures will be modeled by repeated measures and fitting random effects models with random slopes. Random effects models are considered the gold standard when analyzing repeated measures and handling missing data in longitudinal design [59, 60].

Baseline characteristics as mean with standard deviation or median with interquartile and frequency with percentage will be described for the four participant groups, active and sham. The change from the first to second data points will be calculated for the 14-day treatment session in regard to HRV and NRS present pain intensity. The change from CVI to CVII HRV, NRS present pain intensity, and NRS average pain intensity will be determined. Difference in changes between the groups in the morning session and evening session will be examined and tested by using two-way analysis of variance (ANOVAs) or random intercept and slope models. For overall difference in the changes between the four groups regardless of morning, evening or days, random intercept models or repeated one-way analysis of variance (ANOVAs) will be used to analyze the data. The tests will be two-sided, and the significance level will be set to 0.05.

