### Design

This study will use a single-blind randomized controlled experimental design which will be reported according to the CONSORT statement [25] and the Guidelines for Reporting Articles on Psychiatry and Heart rate variability (GRAPH) [26] in order to expedite translational research efforts and improve research methods, replication, and peer review [27–29] (Table 1). A total of *N* = 112 consenting FM patients will be consecutively recruited and randomized from the Department of Pain Management and Research at Oslo University Hospital, Ullevål, in Oslo, Norway, during the Summer and Fall of 2019. Participants will be randomized to either an experimental tVNS group, a sham tVNS group, an experimental MNRB group, or a sham MNRB group. Both active and sham treatment interventions will be delivered at home, twice a day, for 15 min in the morning and for 15 min in the evening, for a total duration of 2 weeks (14 days). Treatment adherence to both interventions will be monitored electronically through a portable Android device and from a Daily Treatment Journal. An 80% completion of tVNS stimulation and MNRB training (a completion of 23 treatment sessions out of a total 28) will be regarded as adequate adherence in this project. Participants are invited to the clinic twice for pre- and post-intervention data collection. An overview of the participant selection, study design, and study flow is illustrated in Fig. 1.

**Table 1 Tab1:** World Health Organization Trial Registration Data

Data category	Information
Primary registry and trial identifying number	ClinicalTrials.gov NCT03180554
Date of registry in primary registry	08/06/2017
Secondary identifying numbers	Southeast Regional Health Authority, Norway, Project Number: 2017/766 Cristin Project ID: 619480
Source of monetary and material support	Southeast Regional Health Authority, Norway
Primary sponsor	Southeast Regional Health Authority, Norway
Contact for public queries	[name], M.S., M.A., Ph.D. Fellow Email: [contact]
Contact for scientific queries	[name], M.S., M.A., Ph.D. Fellow Email: [contact] Department of Pain Management and Research Oslo University Hospital, Ullevål
Public title	Body versus Machine: Meditative Breathing versus Vagus Nerve Stimulation in the Treatment of Chronic Widespread Pain
Scientific title	Body versus Machine: Motivational Nondirective Resonance Breathing versus Transcutaneous Vagus Nerve Stimulation in the Treatment of Fibromyalgia

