### Randomization and blinding procedure

#### Randomization

The computer-generated randomized allocation sequencer will be imported into the Viedoc eCRF system and made available to testing administrators. Only testing administrators will have access to participant treatment allocation and the allocation will not be available until the participant has signed the informed consent and deemed eligible to participate in the study.

This investigation will use a list randomization recruitment method [50] for CVI where participants will be randomly allocated to receive one of the four treatment groups: tVNS #1 (active); tVNS #2 (sham); MNRB #1 (active); MNRB #2 (sham). The randomization will be stratified by sex (male = 1, female = 2) and cardioactive medications (yes = 1, no = 0) with varying block size within strata. Viedoc will generate the randomization number as well as the allocated treatment group for each participant.

Participants will be considered as taking cardioactive medication if they report that they are currently taking any medication for high BP, cholesterol, heart disease, or prescription pain medication. Participants will also be considered as taking cardioactive medication if they answer that they use tranquilizers, antidepressants, and/or antipsychotics either “less than every week,” “every week, but not daily,” or “daily.” Participants are permitted to continue taking any previously prescribed pain medications/psychopharmacological treatments that are necessary during the trial period.

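### The seven extra patients per arm are counted both as the dropout allowance and as the source of 0.9 power; if the allowance is used up, power is about 0.81

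*Protocol article*

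**What the plan says.** The relevant text is in the Protocol article, under Statistical considerations and sample size calculation. It defines the effect sizes: "effect sizes of 0.25, 0.5, and 0.9 should be interpreted as small, medium, and large effects", rounded to the nearest 0.05. It gives a base size: "To achieve a statistical power of 0.8 to detect a large effect size, 21 participants are required per group in a case-control study". It then raises that number: "in order to account for possible participant dropout, 28 participants per group will be included which correlates to a statistical power of 0.9". The same section fixes the test level: "The tests will be two-sided, and the significance level will be set to 0.05".

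The Design section gives a total of 112, and the Randomization section describes allocation to one of four groups, so 28 per group is 112 / 4. The article states no dropout rate. It does not say whether the 0.9 refers to patients randomised or to patients with evaluable data.

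**The concern.** The sentence gives the step from 21 to 28 one purpose, to cover dropout, and credits it with a different result, an increase in power from 0.8 to 0.9. A reserve held against dropout is expected to be spent. If it is spent, the analysis has 21 per arm and the power that goes with 21. If the power is to be 0.9, nearly all of the reserve must remain in the analysis and cannot absorb dropout.

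What is at stake is how the result is read. A reader who sees 0.9 attached to a dropout-adjusted sample size will take it as the power after the expected losses. A non-significant active-versus-sham difference would then look like the outcome of a trial with a 10% chance of missing a large effect. At the loss that the inflation implies, that chance is about 19% (1 − 0.81).

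**Working it through.** **Inputs from the article.** Standardised difference d = 0.9; two-sided α = 0.05; 21 and 28 per group; four equal groups (112 / 4 = 28). The two-group comparison of means is taken from the case-control setting that the article cites for its 21.

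**Formula.** For a two-sample t-test with n per group, the degrees of freedom are 2n − 2 and the noncentrality is d × √(n/2). Power is the probability that a noncentral t variable with these parameters exceeds the two-sided 5% critical value in absolute size.

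**Step 1: reproduce the plan's figures.**

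- n = 21: df = 40, noncentrality = 0.9 × √10.5 = 2.92, power = 0.812. With n = 20 power is 0.792, so 21 is the smallest size that reaches 0.8.
- n = 28: df = 54, noncentrality = 0.9 × √14 = 3.37, power = 0.911.

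Both stated pairs reproduce. The normal approximation gives 0.831 and 0.920. A one-sided test would need only 16 and 22 per group, so the figures are two-sided, as stated.

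**Step 2: the dropout that the inflation implies.** The reserve is 28 − 21 = 7 per arm, and 7/28 = 25%. Equivalently, 21 / (1 − 0.25) = 28 exactly. So 28 is precisely the 25%-inflated version of the size for 0.8 power.

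**Step 3: the size needed for 0.9.** n = 26 gives 0.889 and n = 27 gives 0.901. At least 27 evaluable per arm are needed, so one loss per arm (1/28 = 3.6%) is affordable and two are not.

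**Step 4: power after loss from 28 per arm.** The rates are assumptions, because the article gives none.

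| Loss | Evaluable per arm | Power |
|---|---|---|
| 0% | 28 | 0.911 |
| 5% | 26.6 | 0.896 |
| 10% | 25.2 | 0.879 |
| 15% | 23.8 | 0.860 |
| 20% | 22.4 | 0.837 |
| 25% | 21 | 0.812 |

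**Step 5: what a real allowance at 0.9 would take.** Dividing 27 by (1 − loss) and rounding up gives 30 per arm at 10%, 32 at 15%, 34 at 20% and 36 at 25%, that is, 120 to 144 in total against 112. This measures the gap; it is not a recommendation to enlarge the trial.

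**The case against.** The strongest reply is that nothing is miscalculated. Both pairs are right, and the sentence can be read coherently: 21 are needed for 0.8, 28 are enrolled so that 21 remain, and 28 would give 0.9 if everyone stayed. On that reading the design target is 0.8 and it survives the full implied loss. This stands in part. It shows that the sample size is defensible and that the fault lies in what the 0.9 is attached to. It does not rescue the sentence, which ties the 0.9 to a number justified by dropout and gives no condition.

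A second reply is that losses need not remove patients from the analysis. The same section plans random-effects models and carries missing recordings forward, so patients with partial data can still contribute. That is a fair caution about treating 0.81 as exact. But the carry-forward rule for a wholly missed day assumes no change, which can dilute a treatment effect, so it does not restore the 0.9.

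A reader might also infer stronger points that the document does not support:

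- *That 0.9 holds only if nobody drops out.* One loss per arm still gives 0.901, and 5% loss gives 0.896.
- *That 0.9 holds only for one unadjusted test.* The article states 0.05 with no split, so each active-versus-sham test has about 0.91 with 28 per arm. Any multiplicity rule may be in an analysis plan that is not shown. The planned four-group test is not always weaker either: with 28 per arm its power runs from 0.80 to 0.98, depending on the pattern of means.
- *That 28 falls short of the article's own range.* The text "a sample size between 30 and 77 (depending on the HRV metric used) is typically needed" is background from a source not at hand, and it does not say whether the range is per group or in total.
- *That the case-control origin of the effect size is concealed, or that low power at a medium effect is an error.* The origin is stated outright, and the article openly powers for a large effect.

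**Conclusion.** The concern holds as a double use of the same seven patients per arm. The stated 0.9 describes nearly complete follow-up, with at least 27 of 28 evaluable in each arm. If the reserve is used up, power is about 0.81, roughly 0.10 below the 0.911 available with no loss.

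This rests on a two-group t-test at d = 0.9 and two-sided 0.05, on counting only evaluable patients, and on a 25% loss inferred from the step from 21 to 28. A lower actual loss gives a figure between 0.81 and 0.91. The separate figures for 21 and 28 are not wrong, and the trial is not undersized against a 0.8 target. Severity is minor to moderate: the stated power is more favourable than the design delivers after the dropout it allows for, but the sample size, endpoint and analysis are unaffected.

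**What to change.** Replace the unqualified 0.9 with a statement that ties each power figure to a number of evaluable patients, for example:

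> 28 per arm are randomised. Allowing up to 25% dropout (21 evaluable), each active-versus-sham comparison has about 81% power for d = 0.9 at two-sided 0.05; without dropout it is about 91%.

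If the sponsor assumed a different dropout rate, that rate and the matching power from the table should be given instead. The sponsor should also confirm that active versus sham is the comparison that the figure is meant to describe.

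The cost is a change of wording and a less favourable headline power. No extra patients are needed, and nothing in the conduct or analysis of the trial changes.

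### The fill-in rules for missing home recordings bias the planned session-change analyses of heart rate variability and pain rating

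*Protocol article*

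**What the plan says.** Everything on this point is in the protocol article, section Statistical considerations and sample size calculation. Four home recordings are planned per day: before and after the morning session, and before and after the evening session. Gaps are filled as follows.

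- Morning, before: "If the first (morning pre-intervention) NRS/HRV recording is missing, the last (evening post-intervention) NRS/HRV recording will be used from the night before".
- Morning, after: "If the second (morning post- intervention) NRS/HRV recording is missing, then the first (morning pre-intervention) NRS/HRV recording will be used".
- Evening, before: "If the third (evening pre-intervention) NRS/HRV recording is missing, then the first (morning pre- intervention) NRS/HRV recording will be used".
- Evening, after: "Finally, if the last (evening post-intervention) NRS/HRV recording is missing, then the third (evening pre-intervention) NRS/HRV recording will be used".
- Whole day: "If all morning and evening NRS/HRV recordings are missing from a day, then NRS/HRV recordings from the day before will be used", and this is "based upon the assumption that improvement/change is not present".

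The section then defines what is analysed: "The change from the first to second data points will be calculated for the 14-day treatment session in regard to HRV" and in NRS present pain. Group differences in the morning and evening changes are to be tested by two-way ANOVA or by random intercept and slope models. The change between the two clinic visits (CVI to CVII) is listed as a separate quantity. After a sentence on modelling the patient-reported outcomes with random effects, the section adds: "Random effects models are considered the gold standard when analyzing repeated measures and handling missing data in longitudinal design".

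**The concern.** The copied values feed directly into the quantity being tested. A post-session gap filled with the pre-session value is a change of zero by construction, whatever the session did. A morning baseline filled from the previous night is a value taken after treatment, used as the untreated reference. If sessions produce any change, the mean session change is pulled away from its true value, and the pull depends on how many recordings each arm loses. The Limitations section accepts that participants may recognise which version they have, so losses need not be equal between active and sham. Copying first also gives up what the section credits random effects models with, namely using incomplete records as they are.

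**Working it through.** **Inputs.** The five fill rules and the session-change analysis are those set out above. The Design section counts 23 of 28 sessions as adequate adherence. Check: 80% of 28 is 22.4, rounded up to 23, and 23/28 = 82.1%. No rate of missing recordings is given. I assume 0 to 5 of 28 sessions affected (28 − 23 = 5; 5/28 = 17.9%), which is the range within adequate adherence. It is not a forecast.

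**Step 1: what each gap becomes.**

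| Gap | Filled change |
|---|---|
| Post value only | pre − pre = 0 |
| Morning session, both values | last night's post, used twice: 0 |
| Evening session, both values | morning pre, used twice: 0 |
| Morning pre value only | today's post − last night's post |
| Whole day | yesterday's two changes, repeated |

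One missed session scores 0. Two missed on the same day score yesterday's full effect. (The first morning has no previous home evening to copy from; this is a minor gap.)

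**Step 2: shrinkage within an arm.** With true mean change δ and a share m of sessions with an isolated missing post value, the filled mean is (1 − m)δ. At m = 0 this is 100% of δ; at m = 5/28 it is 23/28 = 82.1%. If the five missed sessions are instead two whole days plus one single session, only the single one becomes zero, giving 27/28 = 96.4% under a steady effect.

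**Step 3: difference between arms.** The filled difference is (1 − m_A)δ_A − (1 − m_S)δ_S. Units are arbitrary. For comparison, the rules were applied literally and in order to simulated data: 14 days of 4 recordings, 40,000 participants per arm, gaps at random, steady effect.

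| δ_A, δ_S | Arms with 17.9% of post values missing | True | Formula | Simulated |
|---|---|---|---|---|
| 0.50, 0 | both | 0.50 | 0.821 × 0.50 = 0.411 | 0.411 |
| 0.50, 0.20 | both | 0.30 | 0.821 × 0.30 = 0.246 | 0.245 |
| 0.50, 0.20 | active only | 0.30 | 0.411 − 0.20 = 0.211 | 0.208 |
| 0.50, 0.20 | sham only | 0.30 | 0.50 − 0.164 = 0.336 | 0.337 |
| 0.20, 0.20 | active only | 0 | −0.20 × 5/28 = −0.036 | −0.037 |
| 0.20, 0.20 | sham only | 0 | +0.20 × 5/28 = +0.036 | +0.036 |

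The mean of the observed session changes stayed within 0.002 of the truth in all six rows.

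**Step 4: other gap patterns.** For a true difference of 0.50 and 17.9% missing in both arms, the filled difference was 0.43 for whole sessions and 0.45 for pre values only. It was 0.50 for whole days. With an effect that grows over the 14 days, whole-day copying gave 0.485. The plain mean of observed changes gave 0.493 there, so only part of that shortfall is due to copying.

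**Step 5: duplication.** If the whole-day rule is applied to someone who stops after day 3, 28 − 6 = 22 of 28 sessions (79%) are copies of day 3, entered as if observed.

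**The case against.** **The main result may not be affected.** A reader might infer that the primary HRV result is biased. The documents do not support that. The rules concern the daily home recordings, while the CVI to CVII change has its own clinic measurements. The Abstract names HRV change as the primary outcome without saying which of the two changes is meant. This objection stands, and the point is limited to the home-session analyses.

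**Zero is a fair value for a session not performed.** This is partly right: no session, no acute change. But the same rules also cover sessions that took place and lost a recording, and the whole-day rule credits yesterday's effect to two sessions that may not have happened. One convention cannot justify both.

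**The whole-day rule does what it says.** Its rationale can be read as no change from one day to the next, which copying yesterday does encode. It also caused no mean bias under a steady effect. This stands as far as the mean is concerned, so it would be wrong to say that every missing recording pulls the estimate toward zero.

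**The conflict with the random effects sentence is partial.** That sentence follows one about patient-reported outcomes, so it covers NRS and does not clearly cover HRV. ANOVA also remains an option for session changes. This stands, and it means the fix must choose the model.

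**The sizes depend on an assumed rate.** True. The 5 of 28 limit is a threshold for one participant, counted in sessions, and not an expected average over recordings.

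**Conclusion.** The concern holds for the home-session change analyses of HRV and NRS. As written, the rules set some changes to exactly zero, use a treated value as a morning baseline, and score a missed session and a missed day on different assumptions.

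Over the assumed range of 0 to 5 of 28 sessions with an isolated missing post value, the mean session change falls to between 100% and 82% of its true value. With unequal gaps the error can go either way: if both arms truly change by 0.20, one arm missing 17.9% of post values produces a false difference of about 0.036 against that arm. There is no bias if neither arm changes, or if equal changes meet equal gaps. These figures assume gaps at random and a steady effect. Whole-day copying adds little mean bias under a steady effect but treats duplicates as data. Its effect on standard errors was not calculated.

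A reader might also infer a definite loss of trial power. That would require the design effect size of 0.9 to refer to the session change, with the standard deviation unaffected by filling. The article states neither.

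**What to change.** For the daily session analyses, delete the substitution rules from the main analysis. Name the random intercept and slope model, now listed as an alternative to ANOVA, as the method for both HRV and NRS. Fit it to all observed recordings without fill-in, and state that this is valid under missing at random. If the copying rules are kept at all, label them as a sensitivity analysis. Make the change before the unblinded export.

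The cost is a few lines of analysis wording and a commitment to one of two models already named. Data collection, software and sample size do not change.

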#### ViedocMe

Participant-reported outcome measures (PROMs) in the form of questionnaires (see below) will be completed electronically using the ViedocMe functionality available in Viedoc at CVI and CVII. Study staff will create a ViedocMe account for each participant in the participant’s Clinic View in Viedoc and provide a unique log-in profile (username, pin code, and ViedocMe web address) for each participant. Participants are to use this information to log in to their personal ViedocMe account on a tablet (Samsung Galaxy Tab A6 32GB) which is connected to Oslo University Hospital’s secure wireless account. The questionnaires in ViedocMe will only be available for completion the day of each clinic visitation. Participants will complete the questionnaires at the end of each visitation. After the time-window has expired (i.e., at midnight on the day of the clinic visit), questionnaires can no longer be completed electronically. If problems arise using ViedocMe, or if the participant prefers to use paper forms, paper copies of the questionnaires will be handed out to the participant and the data will be entered into Viedoc by testing administrators. Questionnaires are only available to participants in Norwegian. For a list of names with descriptions of each questionnaire utilized in this study, see the Appendix.

List of questionnaires in the order of their completion:

Credibility Expectancy QuestionnaireParticipant Global Impression of ChangeEQ-5D-5LHopkins Symptom ChecklistMultidimensional Assessment of Interoceptive Awareness, version 2Spiritual and Religious Attitudes in Dealing with IllnessPain catastrophizing scaleBrief Pain InventoryInsomnia Sleep InventoryOswestry Low Back Pain Disability QuestionnaireGeneral Health Questionnaires

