#### Patient Global Impression of Change

The Patient Global Impression of Change (PGIC) is a self-report measure of a patient’s belief about the efficacy of a treatment and their overall improvement. Patients rate their change on a 7-point scale: “very much improved,” “much improved,” “minimally improved,” “no change,” “minimally worse,” “much worse,” or “very much worse” [132]. Despite a weak positive correlation between PGIC and improvement in standard FM/CWP outcome measures, the PGIC is still believed to be an important source of patient-reported symptoms and a clinically relevant tool in the assessment of perceived impact of FM disease management [133]. The PGIC is especially helpful when paired with other domain-specific questionnaires and/or items following interdisciplinary psychologically based treatments for pain [134]. The PGIC will only be delivered during clinical visitation II.

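### Random slopes are specified for questionnaires measured at most twice, and a two-way ANOVA with no stated patient effect is allowed for up to 28 sessions per patient

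*Protocol article*

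**What the plan says.** All of the model text is in the protocol article under Statistical considerations and sample size calculation.

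- **Patient-reported outcomes.** "The patient-reported outcome measures will be modeled by repeated measures and fitting random effects models with random slopes". No outcome is excepted.
- **Session changes.** Changes in HRV and present pain across treatment sessions are compared between groups for morning and evening sessions, to be "tested by using two-way analysis of variance (ANOVAs) or random intercept and slope models".
- **Overall four-group comparison.** A random intercept model or a one-way ANOVA described as repeated.
- **Test level.** "The tests will be two-sided, and the significance level will be set to 0.05".

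The measurement schedule is given elsewhere.

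- The ViedocMe section says that the questionnaires "will be completed electronically using the ViedocMe functionality available in Viedoc at CVI and CVII", and Table 2 shows at most these two occasions.
- The Appendix gives the CEQ at CVI only. For the other single measurement it says: "The PGIC will only be delivered during clinical visitation II".
- The Appendix also lists the NRS among the patient-reported measures, recorded four times a day at home.
- The Design section counts 28 treatment sessions per patient over 14 days.

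**The concern.** Two statements about models do not match the schedule.

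First, a random slope describes how patients differ in their trend over time. Two measurements per patient cannot separate that variation from residual noise, and one measurement contains no trend at all.

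Second, session changes are clustered within patients. A two-way ANOVA of group by session type with no patient term treats each session as a new, independent observation. Its standard errors are then too small, and a chance difference between active and sham can be declared significant. HRV is the primary outcome and session changes in HRV are among the data analysed this way, so the matter reaches beyond secondary questionnaires.

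The missing-data rule can add to the clustering: when a whole day is missing, the previous day's recordings are reused, which duplicates that patient's session changes.

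**Working it through.** **Sample size, for reference.** Inputs from the article: "effect sizes of 0.25, 0.5, and 0.9 should be interpreted as small, medium, and large effects"; "To achieve a statistical power of 0.8 to detect a large effect size, 21 participants are required per group in a case-control study"; "28 participants per group will be included which correlates to a statistical power of 0.9". A two-sample t-test with d = 0.9 and two-sided 0.05 needs 20.4, rounded up to 21, per group for power 0.8. With 28 per group the power is 0.911. Both stated figures reproduce. They rest on a two-group comparison, and nothing below changes them.

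**Random slopes with two occasions.** Code CVI as t = 0 and CVII as t = 1. Let a be the intercept variance, b the slope variance, c their covariance and s the residual variance. Then:

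- Var(CVI) = a + s
- Cov(CVI, CVII) = a + c
- Var(CVII) = a + 2c + b + s

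These are three equations in four unknowns (rank 3 of 4). Two different parameter sets show the consequence:

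| a | b | c | s | Var(CVI) | Cov | Var(CVII) |
|---|---|---|---|---|---|---|
| 0.5 | 0.4 | 0 | 0.3 | 0.8 | 0.5 | 1.2 |
| 0.7 | 0.8 | -0.2 | 0.1 | 0.8 | 0.5 | 1.2 |

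The data cannot tell the two apart, although the slope variance doubles and the residual variance falls to a third. With three or more occasions the rank is 4 of 4, so the daily series supports the model.

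A trial fit to simulated data (112 patients, two occasions, a time effect only) converged without a warning. The means are still estimated, but the split between slope and residual variance that it reports is arbitrary.

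**Two-way ANOVA on session changes.** Inputs: 28 patients per group; 28 sessions, or 14 if only mornings or only evenings are used; nominal 0.05. The article gives no within-patient correlation of session changes, so an ICC range is assumed. With m sessions per patient entered as independent:

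- Design effect: DEFF = 1 + (m - 1) x ICC
- Two-group type I error: 2[1 - Phi(1.96/√DEFF)]

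Example with m = 14 and ICC = 0.1: DEFF = 1 + 13 x 0.1 = 2.3; 1.96/√2.3 = 1.29; error = 0.20.

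The four-group figures come from simulating a group by morning/evening ANOVA with no true effect (4 x 28 patients, 28 sessions, 4000 runs).

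| Assumed ICC | DEFF, 14 sessions | Error, two groups | DEFF, 28 sessions | Error, four groups |
|---|---|---|---|---|
| 0.05 | 1.65 | 0.13 | 2.35 | 0.34 |
| 0.1 | 2.30 | 0.20 | 3.70 | 0.55 |
| 0.2 | 3.60 | 0.30 | 6.40 | 0.76 |
| 0.3 | 4.90 | 0.38 | 9.10 | 0.83 |

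At ICC 0 the simulated four-group error is 0.05, and at ICC 0.02 it is already 0.16. One mean per patient over the same 28 sessions gives 0.044 to 0.054 at every ICC from 0 to 0.7. Averaging to one morning and one evening value while still ignoring the patient is not enough: in four groups the error is 0.07 at a correlation of 0.1 and 0.16 at 0.5.

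**The case against.** The case on the other side is substantial, and much of it stands.

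- **The treatment comparison of the questionnaires is not broken.** With two occasions, a correlated intercept and slope plus a residual generates the same 2 x 2 covariance as an unstructured model. Only a nuisance split is arbitrary. A reader might infer that the model will fail or that its treatment test is invalid; the documents and the algebra do not support that. This stands.
- **The text states no intercept-slope covariance.** Without one there are three parameters for three moments. This stands in part. Under the coding above, the slope variance is then simply Var(CVII) minus Var(CVI), which is hardly what a random slope is meant to capture.
- **The NRS is also a patient-reported outcome.** Its daily series supports random slopes. This stands, and it is why the sentence needs dividing rather than deleting.
- **CEQ and PGIC are measured once, so a repeated-measures sentence cannot sensibly mean them.** This is fair, but the sentence makes no exception.
- **The ANOVA might include a patient term or use patient summaries.** This stands as a condition on the inflation. The one-way option is called repeated and can be read as a valid repeated-measures ANOVA. The two-way option carries no such word.
- **Each ANOVA option sits beside a mixed model that handles repeated sessions, and changes from CVI to CVII give one value per patient.** Both stand. A reader might conclude that the planned models do not fit the data at all; that is too broad.
- **The choice may be settled in an analysis plan not shown.** This is possible. A reader might also infer that the method will be picked after seeing results. The article does not say so, and it assigns the initial main analysis to an independent statistician blinded to allocation. Blinding does not, however, correct a standard error that ignores clustering.

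**Conclusion.** The point holds in a limited form.

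The random-slope sentence is too wide. For questionnaires measured at CVI and CVII, slope and residual variance cannot be separated when intercept and slope are correlated; for CEQ and PGIC there is no slope to model. The harm is confined to the variance components.

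The two-way ANOVA option is the more serious part, because the article permits it for clustered session data without stating a patient effect. The inflation depends on two things: that this option is chosen, and that sessions are entered as independent. Under those conditions the error is several times nominal over most of the assumed ICC range, and it is above nominal even at ICC 0.02. The ICC values are assumptions. The mixed-model alternative, a repeated-measures ANOVA and an analysis of one value per patient do not have this problem.

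**What to change.** Change the analysis wording before the unblinded data are released.

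1. Restrict random slopes to the daily NRS and HRV series.
2. For outcomes measured at CVI and CVII, use ANCOVA of the CVII value adjusted for the CVI value, or a two-occasion model without a random slope.
3. Compare PGIC between arms as a single measurement, and use CEQ as a single baseline measure.
4. For session changes, name one primary mixed model with a patient random effect, arm and morning/evening session.
5. Drop the two-way ANOVA option. If an ANOVA is kept, state that it is a repeated-measures ANOVA or uses one summary value per patient.

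The cost is a revision of a few sentences. No data collection changes, and the sample size stays as it is.
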